#### Myocardial infarction:

- Re-infarction is defined by recurrent symptoms and/or new electrocardiographic changes, in association with re-elevation of the creatine kinase (CK) of > 1.5 times the previous value with elevation of CK-MB, if within 48 h, or > 3 times the upper normal limit, if after 48 h from the index infarction.
- More than 5 times the upper limit of normal CK is required for the diagnosis of myocardial infarction after bypass surgery.

#### Target vessel revascularization(TVR):

- TVR is defined as any repeat percutaneous intervention or by-pass grafting of the target vessel previously treated successfully with the stent.

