#### *Possible advantage of Xience V stent over other DES*

1. The Xience V stent has very thin stent struts (81 µm) compared to the Cypher stent (134 µm).

It has been shown before for bare metal stents, that strut geometry and thickness influence the vessel wall injury and neointimal proliferation. Less extensive vessel wall injury during stenting with thin strut stents may influence the time-table of wound healing response and restoration of endothelial function.

2. This thinner strut thickness and lower crossing profile of the Xience V stent compared to the Cypher stent increases the deliverability success of the stent, especially in tortuous and calcified lesions, as well as in distal lesions. Moreover, lower profile may decrease the risk

of polymer damage during delivery, as was recently shown with scanning microscopy for a Cypher stent of which delivery through another stent had failed.

3. The non-erodable two polymers used on the Xience V stent are acrylic and fluoro polymers, biocompatible and already used for years in vascular sutures. They may result in less inflammatory reaction after stent implantation. Less inflammatory response or shorter inflammatory response may also have a beneficial influence on vascular healing and neointimal proliferation.

4. In animal models, delayed arterial healing and poor re-endothelialization was demonstrated after oral everolimus in a rabbit model of iliac artery stent implantation. Despite the fact that low dose everolimus did not show these effects, the suppression of neointima was similar in the high and low dose group. This suggests a wide therapeutic window and the possibility to keep the detrimental effects on vascular wall healing limited together with effective suppression of neointimal proliferation. In fact, recently, Finn et al. demonstrated almost complete endothelialization of a Xience V stent with even tight intercellular junctions, 14 days after implantation in a porcine coronary artery. This was in contrast to poor endothelialization of the TAXUS stent in the same model.

The issues raised above provide the rationale for testing the performance of the Xience V stent in patients with acute myocardial infarction and in all comers.

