### 5.1.1 Endpoint of the Study

The **primary endpoint** of the study is to assess the 12 month MACE (cardiac death, non-fatal MI, TVR) in all MCL PCI patients comparing the Xience stent to the CYPHER stent.

The **secondary endpoints** are:

- (Sub)-acute stent thrombosis (SAT) at 30 days and late stent thrombosis (LST) at 1, 2 and 3 year. (Definite and Probable, according to ARC definition). Possible stent thrombosis will be reported separately.
- Clinical MACE at 30 days and 2 and 3 years (cardiac death, non-fatal MI, TVR).
- All cause mortality at 1,2 and 3 year.
- Inability to deliver Cypher or Xience stent (cross over)

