#### Major Adverse Cardiac Events (MACE):

- MACE is defined as any event during follow-up in hierarchical order: cardiac death, non-fatal re-infarction or TVR.

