### ***6.2 PREPROCEDURAL SCREENING.***

The patients are screened for inclusion and exclusion criteria before offering enrolment in the study. The patient should be informed on the study objectives and the required post procedure follow-up. The patient will provide witnessed oral consent before and sign the informed consent before or after the procedure.

Pre-procedure following is collected:

1. Demographic documentation
2. Clinical examination and clinical history
3. Blood analysis

The patient is considered enrolled in the trial when all selection criteria are met and the randomization envelop has been opened (**after the diagnostic angiogram**).

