### ***7.4 Stent implant***

The stent should be selected on the basis of the lesion length. The stent length must exceed the target lesion length by 5 mm (2,5 mm on each site). Direct stenting or pre-dilatation is at the discretion of the operator.

If multiple stents need to be implanted, the stent belongs to the same group as previously randomized.

Residual stenosis, after the stent implant, must be less than 30%. In those cases where the result is not optimal it is requested to postdilate the stent.

The implant procedure is considered successful if the residual stenosis is less than 30% with TIMI flow III.

If there are coronary dissections at the end of the stenting procedure, they must be treated with an additional stent from the same randomization group.

When stent implantation is not successful, cross-over to the other stent of this study or bare stent or balloon only, is allowed.

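### The TVR component of primary MACE counts only vessels stented successfully, a result known only after randomisation and expected by the protocol to favour one arm

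*Protocol*

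**What the plan says.** The primary endpoint (protocol, section 5.1.1) is to "assess the 12 month MACE (cardiac death, non-fatal MI, TVR) in all MCL PCI patients comparing the Xience stent to the CYPHER stent". Section 5.1.2 builds the composite: "MACE is defined as any event during follow-up in hierarchical order: cardiac death, non-fatal re-infarction or TVR". The TVR component carries a restriction of its own: "TVR is defined as any repeat percutaneous intervention or by-pass grafting of the target vessel previously treated successfully with the stent". The TLR definition has the same restriction, but TLR is not part of the primary endpoint.

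Three other places bear on it:

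- Section 6.2 fixes enrolment at the opening of the envelope, after the diagnostic angiogram and so before stenting: "The patient is considered enrolled in the trial when all selection criteria are met and the randomization envelop has been opened".
- Section 7.4 gives a criterion for success, "The implant procedure is considered successful if the residual stenosis is less than 30% with TIMI flow III", and provides for failure: "When stent implantation is not successful, cross-over to the other stent of this study or bare stent or balloon only, is allowed".
- Section 2, on the possible advantages of Xience V, expects the arms to differ: "This thinner strut thickness and lower crossing profile of the Xience V stent compared to the Cypher stent increases the deliverability success of the stent". Failure to deliver the allocated stent is also a secondary endpoint in section 5.1.1.

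**The concern.** A component of the primary endpoint depends on something that happens after allocation and that the allocated device can influence. If an implant fails and the patient later needs repeat PCI or bypass of that vessel, the event does not meet the definition of TVR. The restriction acts on the events and not on the patients: the endpoint is to be assessed in all PCI patients, and nothing in the protocol takes failed implants out of the denominator. Such a patient is therefore scored as free of TVR in that vessel.

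The arm with more failed implants has more of its later TVR removed. On the protocol's own expectation about delivery, that arm is Cypher. The TVR comparison would then look less favourable to Xience than it should, and the later cost of failed delivery would be missing from the endpoint meant to show it. A larger sample does not reduce this bias.

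**Working it through.** The protocol has no figure to reproduce: section 5.2.1 says that no sample size calculation was made, and no failure rate is given anywhere. The check has two parts.

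**1. Which events are lost**

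- Vessel left with a bare stent or balloon only: a later TVR is not counted.
- Study stent placed but result unsuccessful: a later TVR is not counted.
- Successful cross-over to the other study stent: not counted if the definition means the assigned stent, counted if it means either study stent. The text does not settle this.
- Cardiac death or MI after a failed implant: counted as usual.

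**2. Size of the shift in the TVR difference**

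Let f be the share of patients with an unsuccessful implant (fC for Cypher, fX for Xience), p the one-year TVR rate after success (the same in both arms) and q the one-year TVR rate after failure. Each patient is treated as having one target vessel.

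- TVR with all events counted: (1 − f)p + fq
- TVR as written: (1 − f)p
- Shift in the Xience minus Cypher difference: q(fC − fX), which is positive (against Xience) when fC > fX

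Assumed ranges, none of them from the documents: fC 3-8%, fX 1-3%, q 10-20%. The number per arm, 1000, is from the study summary.

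| fC | fX | q | Cypher TVRs lost per 1000 | Xience TVRs lost per 1000 | Shift (points) |
|---|---|---|---|---|---|
| 3% | 3% | 10-20% | 3-6 | 3-6 | 0 |
| 3% | 1% | 10% | 3 | 1 | 0.02 × 10% = 0.20 |
| 5% | 2% | 15% | 7.5 | 3 | 0.03 × 15% = 0.45 |
| 8% | 3% | 20% | 16 | 6 | 0.05 × 20% = 1.00 |
| 8% | 1% | 20% | 16 | 2 | 0.07 × 20% = 1.40 |

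The ranges therefore give 0 to 1.4 points. For scale, the 95% CI half-width for a difference in MACE at an assumed 9% in both arms is 1.96 × √(2 × 0.09 × 0.91 / 1000) = 2.51 points. The middle case is 0.45 / 2.51 = 0.18 of that, and the extreme case 1.40 / 2.51 = 0.56.

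**Illustration of sign.** Take p = 5.6%, the one-year TVR with a sirolimus stent that section 2 cites from a randomised STEMI trial, and assume fX = 1%, fC = 3%, q = 20%.

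- All events counted: Xience 0.99 × 5.6% + 0.01 × 20% = 5.74%; Cypher 0.97 × 5.6% + 0.03 × 20% = 6.03%; difference −0.29 points.
- As written: Xience 5.54%, Cypher 5.43%; difference +0.11 points.

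The sign reverses, although both differences are small against the half-width. Excess risk after failure is not needed for bias: with q = p = 5.6% the true difference is 0 and the wording produces 0.02 × 5.6% = 0.11 points.

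**The case against.** The case against has several parts, and much of it stands as a limit on the point.

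- **The primary comparison as a whole.** A reader might infer that the randomised comparison of MACE is invalidated. The documents do not support that. Cardiac death and MI count whatever the implant result, the patients stay in the denominator, and a failed-implant patient whose repeat procedure accompanies an MI or cardiac death still has a MACE. So does a patient with a counted TVR in another, successfully stented vessel. The TVR figures are therefore upper bounds for MACE.
- **Cross-over.** A reader might infer that no crossed-over patient can ever have a TVR. That holds only if the definition means the assigned stent.
- **The success criterion.** Section 5.1.2 does not refer to section 7.4. Reading the residual-stenosis and TIMI-flow criterion into the TVR definition is plausible but inferred. Under any reading, success is judged after allocation.
- **The predicted imbalance.** Section 2 gives only a direction, and only for delivery. It does not say that residual stenosis or TIMI flow will differ by arm, or that failures carry a high risk of repeat revascularisation.
- **Visibility.** Failed delivery is reported by arm as a secondary endpoint, so it is not wholly hidden. What is lost is the later TVR of those patients within MACE.
- **The SAP.** An SAP not shown here may set an intention-to-treat population, and its absence from the protocol is no finding. It would not cure this: it fixes who is analysed, while the event would still fail the definition.

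**Conclusion.** The defect is real but limited to the TVR component. The definition makes that component depend on a result that follows randomisation, and nothing else in the protocol overrides it. If Cypher delivery fails more often, as section 2 leads one to expect, the component is biased against Xience.

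The size cannot be determined from the documents. Under the assumed failure and TVR rates it is 0 to 1.4 points in the TVR difference, 0.45 in the middle case, and no more than that in MACE. It may be negligible if failures are rare or evenly split. A reader might take the sign reversal as a prediction that the trial's conclusion would change; it shows only that the wording can affect the direction of a small difference.

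**What to change.** In section 5.1.2, define TVR as any repeat PCI or bypass grafting, after the index procedure, of any vessel in which treatment was attempted at the index procedure. It should apply regardless of the device used, cross-over or procedural success, with the event counted in the randomised arm.

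The new wording must also say how two situations are classified, with the same rule in both arms: staged procedures already planned at the index procedure, and immediate completion of a failed index attempt. Without this, the broader definition would turn them into primary events.

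Make the same edit to TLR. TVR after successful implantation can be kept as a supplementary result.

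No new outcome data are needed, because section 9 already provides for collecting every repeat intervention, surgical or percutaneous. The cost is a slightly higher event rate and the work of classifying planned staged procedures.

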#### Target lesion revascularization (TLR):

- TLR is defined as any repeat percutaneous intervention or by-pass grafting of the target lesion previously treated successfully with the stent or the 5 mm proximal or distal to this initial lesion.

#### Major Adverse Cardiac Events (MACE):

- MACE is defined as any event during follow-up in hierarchical order: cardiac death, non-fatal re-infarction or TVR.

## **5.2        *Patients selection criteria***

The patient population must be geographically stable and able to perform the follow-up examinations at or by the Investigation Centre. Patients who are not willing or unable to participate in the follow-up will not be enrolled in the study.

### **5.2.1 Number of patients**

A total number of 2000 consecutive patients fulfilling the inclusion/exclusion criteria and willing to sign the informed consent can be enrolled in the trial.

This study is a clinical outcome study in 2000 all comers during the period 2007-2008 and runs parallel with the XAMI trial in which 800 patients are included. Since all types of outcome are expected no sample size calculation is performed.

### **5.2.2 Study duration**

The duration of the enrolment period will terminate when a total of 2000 patients will be enrolled and is estimated to last 18 months.

With a follow-up period of 36 months, the total study duration will be 54 months.

### **5.2.3 Enrolment criteria**

#### Inclusion criteria

- 1) Patient is willing to sign the informed consent
- 2) Patient is willing to perform all follow-up examinations as required by the protocol
- 3) Patient eligible for coronary revascularization intervention by PCI and stenting
- 4) Patient is located in a geographic area that will enable contact by the study site for follow-up.

#### Exclusion criteria

- 1) Patients who are minor, intravenous drug abusers, alcohol abuser, prisoners or unable to give informed consent

- 2) Patients who are allergic to everolimus or sirolimus
- 3) Patients with known intolerance or contra-indications to treatment with acetylsalicylic acid or clopidogrel
- 4) Patients in whom the cardiologist judges that stent implantation is not possible, realistic or justified.

## **6. CONDUCT OF THE CLINICAL STUDY**

### ***6.1 GENERAL ASPECTS.***

The study will be performed in accordance with the European Regulation EN 14155 part 1 and 2. Respect of patient's rights will be granted during the trial phase according to the most recent version of the Helsinki Declaration.

### ***6.2 PREPROCEDURAL SCREENING.***

The patients are screened for inclusion and exclusion criteria before offering enrolment in the study. The patient should be informed on the study objectives and the required post procedure follow-up. The patient will provide witnessed oral consent before and sign the informed consent before or after the procedure.

Pre-procedure following is collected:

1. Demographic documentation
2. Clinical examination and clinical history
3. Blood analysis

The patient is considered enrolled in the trial when all selection criteria are met and the randomization envelop has been opened (**after the diagnostic angiogram**).

## **7. STUDY PROCEDURES AND METHODS**

Direct stenting or pre-dilatation is at the discretion of the operator.

### ***7.1 Percutaneous access***

Preparation of the access site and percutaneous access should be performed according to the normal hospital practices. Heparin should be administered intravenously to obtain an ACT of 300 sec or more.

### ***7.2 Diagnostic angiographic examination***

The diagnostic angiographic examination should be performed in order to identify the vessels affected by atherosclerotic lesions.

### ***7.3 Randomization***

Randomization will be done by closed envelopes. The investigator chooses the envelope to the following sequential number available. The randomization code should be recorded on the CRF and notification form.

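### Allocation by investigator-taken closed envelopes has no record tying patient to envelope before opening, and the protocol dates enrolment in two conflicting ways

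*Protocol*

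**What the plan says.** Only the protocol is at hand. Its provisions on this point are:

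- **Method (Section 7.3).** "Randomization will be done by closed envelopes. The investigator chooses the envelope to the following sequential number available". On documentation the section adds only this: "The randomization code should be recorded on the CRF and notification form".
- **What is known by then (Sections 7.2 and 6.2).** The angiogram comes first: "The diagnostic angiographic examination should be performed in order to identify the vessels affected by atherosclerotic lesions". Section 6.2 states in bold that the envelope is opened after it.
- **Enrolment, first definition (Section 6.2).** "The patient is considered enrolled in the trial when all selection criteria are met and the randomization envelop has been opened".
- **Enrolment, second definition (Section 14).** A patient can be considered enrolled once the criteria are met and the consent form is signed. Where signing beforehand is not feasible, the signature may follow the procedure, with oral consent given before it.
- **Purpose (Section 2, rationale for all comers).** Randomisation is what is meant to make the comparison of the two stents unbiased.

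The protocol describes no blinding. It does not say that the envelopes are opaque, who prepares or holds them, or that anything is written down before one is opened.

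**The concern.** Concealment means that nobody deciding on a patient's entry can know or alter the coming allocation. Here the investigator handles the envelopes, the lesions are already visible, and no entry made beforehand commits a particular patient to a particular envelope. An envelope could be read in advance, or two patients' envelopes exchanged, without any pre-opening record that would show it.

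The two enrolment definitions add a second gap. If enrolment waits for a signature after the procedure, a patient whose stent type is already known may never enter the count.

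Selection bias of either kind cannot be repaired in the analysis. It therefore has to be prevented in the allocation procedure, which this protocol fixes in Section 7.3 itself.

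**Working it through.** **1. The passages side by side**

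| Step | Protocol | Commitment before allocation is known |
|---|---|---|
| Screening, demographics, witnessed oral consent | 6.2 | Patient identified, but not linked to an envelope number |
| Angiogram | 7.2 | Diseased vessels seen; no intended target recorded |
| Next numbered envelope taken and opened | 7.3, 6.2 | None required |
| Code entered on CRF and notification form | 7.3 | Order and time relative to opening not stated |
| Signed consent, possibly after the procedure | 14 | Comes after allocation is known |

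Sequential numbering fixes the order on paper. Gaps or out-of-order use might be found later if the recorded code carries the envelope number, but no such reconciliation is required. Reading an envelope in advance and then not offering enrolment would leave no gap at all.

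**2. The two definitions**

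Take a patient who consents orally, has the envelope opened, receives the stent and then does not sign. Under Section 6.2 this patient is enrolled; under Section 14 the patient is not. The protocol does not say which governs.

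**3. Illustrative size**

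There is no planned figure to reproduce: Section 5.2.1 states that no sample size was calculated. From the protocol come 1000 patients per arm (Section 1) and a 1-year MACE of 9.7%, reported in Section 2 for a sirolimus-stent series in STEMI. Everything else is assumed.

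Suppose *m* allocations are redirected, all one way. Then *m*/2 higher-risk patients are exchanged for *m*/2 lower-risk patients, with risk difference Δ. Each arm moves by (*m*/2) × Δ / 1000, so the arm difference moves by *m* × Δ / 1000.

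- *m* = 60, Δ = 20% − 8% = 12 points: 60 × 0.12 / 1000 = 0.0072, or 0.72 points.
- *m* = 6, same Δ: 6 × 0.12 / 1000 = 0.00072, or 0.07 points.

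For scale, 1000 per arm has 80% power for about 3.4 points at 9.7% MACE (two-sided 5%, assumed), and 0.72 / 3.4 = 21%.

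A second set of assumptions takes 40% complex lesions at relative risk 2 and 9.7% MACE overall. Simple-lesion risk is 0.097 / (0.6 + 0.4 × 2) = 6.93% and complex-lesion risk is 13.86%, so Δ = 6.93 points. A fraction *f* of the 400 complex-lesion patients in one arm is exchanged with simple-lesion patients in the other. With no true stent difference:

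| *f* | *m* = 2 × 400 × *f* | False difference (points) | Type I error, nominal 5% |
|---|---|---|---|
| 0 | 0 | 0 | 5.0% |
| 5% | 40 | 0.28 | 5.5% |
| 10% | 80 | 0.55 | 7.0% |
| 20% | 160 | 1.11 | 13.3% |

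Varying MACE over 7.3% to 14.7%, the complex share over 20% to 40% and relative risk over 1.5 to 3, *f* = 10% gives 5.1% to 13.1% and *f* = 20% gives 5.6% to 37.8%. Small amounts of redirection have small effects; substantial amounts do not.

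**The case against.** The case against is strong on several points, and most of it stands.

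- **Randomising after the angiogram.** This is not a fault. It limits the loss of randomised patients who turn out not to need a stent. It matters here only because nothing is committed before opening.
- **Skipping envelopes.** A reader might infer that the design lets envelopes be skipped. It does not: Section 7.3 prescribes the next number, so skipping would be a breach.
- **Discretionary exclusion.** A reader might infer that an opened envelope can be discarded under the exclusion of "Patients in whom the cardiologist judges that stent implantation is not possible, realistic or justified". Section 6.2 places screening before enrolment is offered and makes opening the moment of enrolment, so the text does not permit this.
- **Direction of bias.** Section 2 says that the Xience V profile "increases the deliverability success of the stent, especially in tortuous and calcified lesions, as well as in distal lesions", which suggests steering difficult lesions towards Xience. But Section 2 also treats Cypher as the reference standard, in routine use at this centre since 2004 with encouraging results. Section 7.4 allows cross-over after a failed implant, which weakens the motive to tamper. No direction can be predicted.
- **Target vessel.** The endpoint wording, "TVR is defined as any repeat percutaneous intervention or by-pass grafting of the target vessel previously treated successfully with the stent", settles the vessel after allocation. That is a question about the endpoint definition, and no size of bias has been shown from it. It supports recording the intended vessel and goes no further.
- **Who opens the envelope.** The protocol says investigator in Section 7.3 and operator in Section 7.4. That they are the same person is an inference, and an implanter cannot be blinded in any case.
- **Existing safeguards.** Sequential numbering, demographic data and witnessed oral consent are real but partial.

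The objection does not remove the absence of any link between patient and envelope before opening, or the conflict between Sections 6.2 and 14. Details such as the block scheme may sit in operating procedures and are not part of this point.

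**Conclusion.** The point holds in limited form. Section 7.3 fixes a method whose concealment depends on compliance alone and leaves no pre-opening record against which compliance could be checked. Sections 6.2 and 14 disagree on when a patient is enrolled, which allows loss after allocation is known.

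The protocol shows that influence is possible. It does not show that influence occurred, in which direction, or how much. The 0.72-point and 0.07-point shifts and the type I error figures rest on assumed redirected shares and risks, and on a MACE rate borrowed from STEMI patients for an all-comer trial. They indicate scale only.

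This is an inexpensive correction worth making, because no later analysis can restore concealment. It is not evidence that the comparison is biased.

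**What to change.** In Section 7.3, require:

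1. Opaque, sealed, serially numbered envelopes, prepared by someone who performs no PCI in the trial.
2. Before opening, catheterisation-laboratory staff already present write the patient number, date, time and intended target vessel(s) on the envelope and in a log.

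Reconcile Sections 6.2 and 14 so that every opened envelope is one randomised patient, followed and analysed in the allocated arm. For a patient who does not sign afterwards, the protocol should state, in agreement with the ethics committee, what data may be kept. The envelope itself should still be counted and reported by arm.

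The cost is about a minute per case, including acute cases, where any delay before opening is least welcome. Someone outside the PCI team is also needed to prepare the envelopes. Stent choice within the arm, the implant procedure and medication are unaffected.
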